### Statistical analysis

Differences in success rate between the groups will be tested with a Chi square test (univariate). Success is defined as at least 30 % pain reduction at 6 months. To account for cluster effects, a linear multivariate mixed model will be used to determine differences in pain score changes over time. A logistic regression model will explore possible predictors for success or failure of the procedure. The changes after 6 months of the outcome variables of the two groups will be compared with a Student’s t-test.

A trial-based economic evaluation will be performed, based on empirical data obtained in the RCT. The base-case economic evaluation will be performed from the societal perspective, including costs inside and outside the healthcare sector and will follow the, in 2012 published, international guidelines [30]. The time horizon of the economic evaluation will be 6 months. The intervention offered in this study is primarily expected to affect morbidity. So, health-related quality of life is considered as an important outcome in these patients. Therefore, a cost-utility analysis will be performed, with the number of quality adjusted life years (QALYs) as the primary outcome measure, based on the EQ-5D. Additionally, a cost-effectiveness analysis from a healthcare perspective will be performed in which pain reduction is used as measure of effectiveness. So, incremental cost-effectiveness ratios will be expressed as 1) the incremental costs per QALY (societal perspective) and the 2) incremental cost per additional patient with a clinically relevant pain reduction (healthcare perspective). The cost analysis will be performed according to Dutch guidelines for cost calculations [30]. Hospital resources use such as outpatient visits and diagnostic procedures will be registered by Case Report Forms. Study-related costs will not be included in the cost-analysis. For costs outside the health care sector, such as visits to the GP, physiotherapist, productivity losses, and out-of pocket costs, patients will be asked to fill out cost questionnaires with a recall period of 3 months at three occasions: at baseline, at 3 months and at the 6-month follow-up. Costs will be calculated by multiplying resources use with standard unit prices [30]. Standard sensitivity analyses (for example, using SF-36 for QALY calculation instead of EQ-5D) and bootstrap analysis will be performed to investigate the uncertainty surrounding the cost-effectiveness ratios. Based on the bootstrap results, cost-effectiveness acceptability curves will be constructed, showing for a wide range of cost-effectiveness threshold values, the probability that IMBI is potential cost-effective. The economic evaluation will only provide insight into the potential cost-effectiveness of IMBI, as IMBI is compared with placebo instead of a natural comparison (CAU). In a secondary analysis, information from the baseline cost questionnaires (covering a period of three months before entering the study), baseline pain scores and baseline quality of life, will also be used as an estimate of costs and effects of CAU.

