**Methods/Design:**

Consecutive discogenic low back pain patients referred to four specialized pain treatment facilities are being screened for eligibility. After a positive standardized provocation discography and informed consent, patients are randomized into two groups. The treatment group receives an intradiscal injection with methylene blue, lidocaine, and contrast, and the control group receives intradiscal isotonic saline with lidocaine and contrast.

Main outcome measures are pain at the 6-month follow-up, patient’s global impression of change, cost-effectiveness, quality of life, disability, and analgesic intake.

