### Objectives

Patients are assessed at baseline, at 6 weeks, 3 months, and at the primary end-point of 6 months, and furthermore, at the follow-up of 12, and 24 months.

Primary outcome measures is average pain at 6 months, measured by a pain diary with numeric rating scales (NRS) three times a day for 4 consecutive days. Success of the intervention is defined as pain reduction of at least 30 % at 6 months.

Other study variables include the Patients Global Impression of Change (PGIC) measured by a 7-point Likert Scale and number of adverse and serious adverse events [26]. Societal cost consisting of hospital cost and costs outside the hospital are measured by means of cost questionnaires. Disability is measured by the Oswestry Disability Index [26], Quality of life (QOL) by the Rand-36 and EQ-5D [26]. Information about pain characteristics is collected using the McGill Pain Questionnaire [26], and information about analgesics use with a diary at each time-point for 4 days. The potential predictive value, for success or failure of the intervention, will be explored with use of baseline variables, MRI classification, and registered variables of the provocative discography [26, 27].

With the exception of the pain and medication diary, and the health-related quality of life EuroQol (EQ-5D) questionnaire, which are presented to the patient in a booklet, all data will be collected by web-based questionnaires software, SelectSurvey. (NETv4.075.011© Copyright 2008 ClassApps.com) and MACRO (version 4.1.2.3750© 1999-2012 InferMed Limited, London, UK).

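### Six-month changes are compared by an unadjusted t-test: valid, but generally less precise than adjusting for the collected baseline values and the stratification factors

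*Protocol article*

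**What the plan says.** The Statistical analysis section names three between-group comparisons. The success rate (at least 30% pain reduction at 6 months) is tested by chi-square. For pain over time, "a linear multivariate mixed model will be used to determine differences in pain score changes over time". Then "The changes after 6 months of the outcome variables of the two groups will be compared" with a Student's t-test. That last sentence does not list its variables and mentions no covariates.

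Baseline values are available: under Objectives, "Patients are assessed at baseline, at 6 weeks, 3 months, and at the primary end-point of 6 months". The measures named there are the pain diary, Oswestry Disability Index, RAND-36, EQ-5D and McGill questionnaire. Randomization and stratification lists four factors: study centre, gender, dichotomised disc level and dichotomised Dallas grade.

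The abstract counts PGIC among the principal outcomes ("Main outcome measures are pain at the 6-month follow-up, patient’s global impression of change"). Under Objectives it is a secondary item: "Other study variables include the Patients Global Impression of Change (PGIC) measured by a 7-point Likert Scale". No test is named for it specifically.

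**The concern.** Subtracting baseline fixes the weight given to the baseline value at exactly 1, whatever the data show. ANCOVA estimates that weight. Unless the true slope happens to be 1, the change score leaves avoidable noise in the treatment comparison, and any chance difference at baseline carries through in part to the result.

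The trial is small, so both effects can matter for the outcomes that describe disability and quality of life. The stratification factors were chosen because the protocol regards them as potential confounders, yet the t-test makes no use of them. PGIC raises a separate, smaller point. It is itself a rating of change, so no change from baseline can be formed for it, and the sentence on changes does not say how it is to be handled.

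**Working it through.** **Number of evaluable patients.** Inputs from the Sample size section: success 50% against 20%, power 80%, significance 5% (taken as two-sided), drop-out 10%. With unpooled variance:

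n = (1.960 + 0.842)² × (0.5×0.5 + 0.2×0.8) / 0.3² = 7.85 × 0.41 / 0.09 = 35.8, so 36 per arm.

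36 / 0.9 = 40 per arm, 80 in total. This reproduces the stated figure. It rests on the binary success endpoint, so the choice between t-test and ANCOVA does not alter it. About 2 × 36 = 72 patients are expected to be evaluable.

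**Relative precision.** Set the 6-month SD to 1 and the baseline SD to k, with within-arm correlation r. The protocol gives neither k nor r, so both are assumptions.

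- Variance of the change score: 1 + k² − 2rk
- Residual variance under ANCOVA (large samples): 1 − r²
- Difference: (1 + k² − 2rk) − (1 − r²) = (k − r)², which is never negative and is zero only when r = k

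Ratio of ANCOVA variance to change-score variance, (1 − r²)/(1 + k² − 2rk):

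| | r = 0.3 | r = 0.5 | r = 0.7 |
|---|---|---|---|
| k = 1 | 0.91/1.40 = 0.65 | 0.75/1.00 = 0.75 | 0.51/0.60 = 0.85 |
| k = 0.8 | 0.91/1.16 = 0.78 | 0.75/0.84 = 0.89 | 0.51/0.52 = 0.98 |
| k = 0.6 | 0.91/1.00 = 0.91 | 0.75/0.76 = 0.99 | 0.51/0.52 = 0.98 |

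At k = 1, if the change-score test had 80% power with 36 per arm, ANCOVA would have 93.5%, 89.9% and 86.0% at the three values of r. Equivalently, it would match the t-test with 24, 27 and 31 per arm.

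**Chance imbalance.** The difference between arms in mean baseline has standard error √(2/36) = 0.24 baseline SDs. Given an imbalance of that size, the change-score estimate is displaced by |k − r| × 0.24 six-month SDs. At k = 1 this is 0.16, 0.12 and 0.07 for r = 0.3, 0.5 and 0.7. At k = 0.6 it is 0.07, 0.02 and 0.02, the last in the opposite direction. ANCOVA removes this displacement.

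**Cost of adjustment.** Baseline takes 1 degree of freedom, four centres 3, and gender, disc level and Dallas grade 1 each: 7 in all. Residual degrees of freedom fall from 72 − 2 = 70 to 70 − 7 = 63.

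**PGIC.** A t-test on the raw 7-point rating was simulated under three assumed response distributions with 36 per arm and 50,000 runs each. Its type I error was 5.0% in each. The 6-month rating can therefore be compared by a t-test; only a change from baseline is undefined.

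**The case against.** The strongest reply is that nothing here is an error. With 1:1 randomisation a t-test on change is valid and unbiased; the displacement above is conditional on an observed imbalance and averages to zero over randomisations. That stands. A reader might infer that the planned test is biased or invalid, and the protocol does not support that.

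A second reply concerns reach. Success, which sizes the trial, is tested by chi-square, and pain is also analysed by a mixed model. That stands too. A reader might infer that every outcome, including the primary one, rests on the t-test, but the protocol gives no list of variables for it. How the mixed model handles baseline is detail an article may leave to the analysis plan.

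A third reply is that the savings often quoted, 35%, 25% and 15%, need equal SDs at both times. Study population requires a pain score of at least 5 at entry, which may narrow the baseline spread for pain. At k = 0.6 the savings shrink to about 9%, 1% and 2%. Likewise, the change score is noisier than ignoring baseline only when r < k/2, which becomes r < 0.5 only at k = 1. This stands and is why a range is shown.

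Finally, a reader might conclude that a t-test cannot be applied to PGIC at all. It can, to the 6-month rating, and comparing that rating is a natural reading of the sentence.

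What the objections do not remove is that the protocol names a specific unadjusted method although better use of data already collected is available. This is a stated choice and not an omitted detail.

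**Conclusion.** The point holds as a matter of efficiency. The unadjusted t-test on 6-month changes is sound under randomisation but generally less precise than a baseline-adjusted analysis, and it ignores the four stratification factors. The loss falls mainly on Oswestry, RAND-36, EQ-5D and McGill.

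Its size is uncertain. ANCOVA variance is between 0.65 and 0.99 of the change-score variance over r from 0.3 to 0.7 and k from 0.6 to 1, all of them assumed. The ratios are large-sample values, so where they reach 0.98 or 0.99 the gain is practically nil. Any further gain from the stratification factors cannot be quantified from the protocol. The success test and the total of 80 are untouched. The PGIC element is a minor clarification.

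**What to change.** Replace the t-test sentence with: each continuous outcome at 6 months is analysed by ANCOVA with treatment, the baseline value of that outcome and the four randomisation factors (centre, gender, disc level, Dallas grade), reporting the adjusted mean difference and its 95% CI.

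Add one sentence for PGIC: the 6-month rating is compared directly between groups, preferably by a proportional-odds model or a rank test.

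The cost is a change of wording and minor programming, plus about seven degrees of freedom among roughly 72 evaluable patients. No additional data are needed. The protocol describes recruitment as ongoing and restricts unblinded data to the monitoring committee's statistician, so the change can be made before the investigators see results by arm.

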### Study population

Consecutive patients with chronic lumbar axial pain referred to the specialized pain centers are assessed for eligibility. Eligibility criteria are a history consistent with lumbar discogenic pain (for example, predominant axial pain produced on lumbar motion, significant functional limitation in sitting duration and tolerance); low back pain for at least 6 months, and in at least the last 6 weeks a poor response to treatment that is, analgesics, physiotherapy, facet blockade and radiofrequency therapy; age between 18 and 66 years; neurological exam without motor deficit; pain intensity of at least 5 measured with the Numeric Rating Scale (NRS) 1 to 10 [20].

Exclusion criteria are discogenic pain confirmed on more than two levels; extruded or sequestered herniated nucleus pulposus; previous lumbar surgery or invasive intradiscal procedures on suspected levels; symptomatic lumbar spinal stenosis; grade 1-2 spondylolisthesis. Further exclusions include BMI (Body Mass Index (kg/m^2^)) of ≥ 35, pregnancy, coagulopathy or oral anticoagulant therapy (except low-dose acetylsalicylic acid) in conditions that do not allow for a temporary discontinuation, and infection. Patients who are incapable of following verbal or written instructions or with psychiatric problems potentially interfering with cooperation in the study will be excluded as well.

Magnetic Resonance Imaging (MRI) must have been performed in the last 12 months before inclusion to rule out severe disc degeneration as evidenced by a > 50 % disc height loss at the affected level [21]. Patients undergo a provocative discography to confirm or rule out discogenic origin of the lumber pain [22–24]. The provocative discography will be conducted according to ISIS/IASP guidelines and with the use of a pressure- and velocity-controlled disc stimulation device (CDS) (Neurotherm™, Wilmington DE, US) [23]. In provocative discography, annular tears according to the Modified Dallas classification of annular tears scheme grade 1 to 4 (see Table 1) in either one, or at most two, discs must be present [13, 21]. Concordant pain provocation must be present in the disc(s) at pressures of less than 50 PSI above opening pressure, of at least NRS 7 (of 10) or ≥ 70 % reproduction of worst spontaneous pain [25]. At least one adjacent lumbar disc should perform as a negative control disc.

**Table 1 Tab1:** Modified Dallas Classification [16]

Grade	Grade Description
0	Contrast is within the nucleus

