### Sample size

The sample size of the RCT is determined on the basis of success rates in the previous RCT [18] and our pilot [28]. We assume that 50 % of patients in the treatment group will be successfully treated. Success is defined as 30 % pain reduction at the 6-month follow-up. In the control group, we assume a 20 % success rate.

Given the invasive character of the IMBI procedure, we consider that the treatment group should be at least 30 % more successful than the control group to reach minimally clinical relevance. Furthermore, we assume 10 % drop out per group.

For a power of 80 % and a level of statistical significance of 5 %, the minimum sample size is under these assumptions estimated to be 80 patients, that is, 40 per randomized group [29].

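### Using patients' own baseline as care as usual fixes its benefit at zero, so natural improvement is credited to IMBI in the secondary economic analysis

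*Protocol article*

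**What the plan says.** All of this is in the economic part of the Statistical analysis section of the protocol article, unless another section is named.

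- **Base case.** IMBI is compared with placebo as randomised. One ratio is cost per QALY (EQ-5D, societal perspective). The other is cost per extra patient with relevant pain relief (healthcare perspective).
- **Horizon.** "The time horizon of the economic evaluation will be 6 months".
- **Cost data.** Questionnaires are completed "with a recall period of 3 months at three occasions: at baseline, at 3 months and at the 6-month follow-up". That gives one 3-month window before entry and two after it.
- **Caveat.** The evaluation is said to show only potential cost-effectiveness, because the comparator is placebo and not care as usual (CAU).
- **Secondary analysis.** To reach CAU, the article turns to the patients' own entry data: "information from the baseline cost questionnaires (covering a period of three months before entering the study), baseline pain scores and baseline quality of life". Of these data it states that they "will also be used as an estimate of costs and effects of CAU".

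Three statements elsewhere bear on this. Study population requires "pain intensity of at least 5 measured with the Numeric Rating Scale". Sample size assumes 50% success on IMBI and says "In the control group, we assume a 20 % success rate". Sample size interim analysis lowers the placebo rate to 10%.

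**The concern.** A baseline value used as the effect of CAU says that a patient left on usual care for 6 months would have exactly the entry pain and entry quality of life. Nobody can then respond under CAU and nobody can gain QALYs. Whatever improvement would have come anyway, through natural course or regression to the mean after entry at a pain threshold, is booked as an effect of IMBI. A randomised trial thereby acquires an uncontrolled before-after comparison.

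The analysis is secondary, but it is the one that addresses the comparator the article itself regards as natural. The Discussion adds that reimbursement in the Netherlands depends on evidence of cost-effectiveness. A reader looking for IMBI against usual care will turn to this figure.

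**Working it through.** **The plan's rates.** Sample size gives 50% v 20%, 80% power, 5% significance (sidedness not stated; two-sided used here) and 10% dropout. With unpooled variance, n = (1.96 + 0.8416)² × (0.25 + 0.16) / 0.30² = 35.8, so 36 per group; 36 / 0.90 = 40 per group, 80 in all. The stated size is reproduced and is not in dispute. It matters here only as the source of the success rates.

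**Responders.** I take relevant pain relief to be the article's success definition, a reduction of at least 30%. Against baseline the reduction is zero for every patient, so the CAU rate is 0%.

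- Gain against baseline-as-CAU: 50 − 0 = 50 points.
- Gain against placebo: 50 − 20 = 30 points, or 50 − 10 = 40 points at the interim rate.
- If IMBI were inert, with 20% responding in both arms: randomised gain 20 − 20 = 0; gain against baseline 20 − 0 = 20 points.

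If the true CAU responder rate is q (an assumption; the article gives none), the overstatement factor is 50 / (50 − q):

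| q (%) | True gain (points) | Factor |
|---|---|---|
| 5 | 45 | 1.11 |
| 10 | 40 | 1.25 |
| 15 | 35 | 1.43 |
| 20 | 30 | 1.67 |

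**QALYs.** If utility under CAU rose linearly by d over half a year, the omitted gain is 0.5 × d / 2. For an assumed d of 0.02 to 0.10 this is 0.005 to 0.025 QALY per patient.

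**Regression to the mean alone.** Assumptions: NRS standard deviation 1.8, unselected mean 5.5 to 6.5, retest correlation r of 0.5 to 0.9, and selection at 5 or more on the same score that serves as baseline. The expected drop is (1 − r) × 1.8 × φ(a)/Φ(a), where a = (mean − 5)/1.8.

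- Mean 5.5, r = 0.5: 0.5 × 1.8 × 0.384/0.609 = 0.57 points.
- Mean 6.5, r = 0.9: 0.1 × 1.8 × 0.282/0.798 = 0.06 points.

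A simulation on the same assumptions gave 0.6% to 18% of patients with a drop of at least 30%, with no true change in anyone.

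**Costs.** Let C be the 3-month baseline cost and k the ratio of post-entry to baseline cost per 3 months, with procedure cost left out. IMBI over 6 months costs 2kC.

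| k | Minus C (CAU unscaled) | Minus 2C (CAU scaled to 6 months) |
|---|---|---|
| 1.0 | +1.0C | 0 |
| 0.7 | +0.4C | −0.6C |

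An unscaled window makes CAU look cheap and counts against IMBI. Scaling removes the length mismatch but leaves the assumption that CAU costs stay flat. That assumption favours IMBI only if CAU costs would have fallen anyway.

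**The case against.** **It is secondary and already hedged.** The randomised comparison is the base case, and the article limits its claims to potential cost-effectiveness. It is true that the base case is untouched. But that caveat is about placebo not being CAU. It does not tell the reader that the CAU estimate allows no improvement.

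**Placebo response is not the course under CAU.** The control injection contains lidocaine, and the Discussion itself doubts whether placebo is the right word. This stands. A reader might infer that the bias is 67%, with cost per responder 40% lower (30/50 = 0.60). That reading equates sham and lidocaine response with CAU, uses only the 20% rate, and needs equal costs. The documents support a range on an assumed CAU rate, not that figure.

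**Regression to the mean may be small.** Patients have had pain for at least 6 months, and the article does not say that the entry NRS is the diary average used as the outcome. If the two differ, the effect shrinks. This limits the size. It does not remove the bias on responders, since a rate fixed at 0% can only be too low. On QALYs the direction requires that CAU patients improve on average.

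**The time windows.** A reader might also infer that the 3-month against 6-month mismatch flatters IMBI. The arithmetic shows the reverse if costs are left unscaled. The article does not say they will be left unscaled, and a scaling rule may sit in the full plan. Nor do the documents show that pre-entry costs were inflated by referral and work-up. Outpatient visits and diagnostic procedures are assigned to Case Report Forms with no stated pre-entry period, while the Objectives section has hospital costs measured by questionnaire, so coverage is unclear. If the baseline questionnaire omits hospital use, CAU cost is understated, again against IMBI.

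**Putting the control arm in place of baseline nearly repeats the base case.** This also stands. It would credit any sham and lidocaine response to CAU. The control arm therefore serves as the other end of a range, not as a replacement.

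**Conclusion.** The point holds on the effect side of one secondary analysis. As written, the plan fixes CAU at 0% responders and no QALY gain, so any improvement that would have occurred under usual care is attributed to IMBI. With IMBI at the planned 50% and an assumed CAU rate of 5 to 20%, the responder gain is overstated 1.11 to 1.67 times, and an inert IMBI could be credited with 20 points. The actual size is unknown, because the article gives no CAU course.

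It does not follow that the cost-effectiveness ratio as a whole favours IMBI. The cost side can run either way, depending on scaling, on what the baseline questionnaire covers, and on how costs would have moved without IMBI. The randomised IMBI versus placebo evaluation is not affected.

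**What to change.** - Present baseline-as-CAU as a no-improvement extreme scenario: the end of the range for effects that is most favourable to IMBI, provided that CAU patients would not worsen on average.
- Show beside it, as the opposite bound, a scenario that uses the control arm's observed 6-month costs and effects with sham-procedure costs removed. State that this may overstate improvement under CAU because of sham and lidocaine response.
- Put baseline costs on the same 6-month basis and state the flat-cost assumption that this makes.
- Draw no conclusion on IMBI versus CAU from the baseline version alone.

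The price is a wider or less favourable secondary figure and a little more analysis. The control arm's data are already planned for the base case, so nothing new has to be collected.
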